### Interpretation of patients' answers

#### Question 1

|              |                                                                                                                                                                                                                                                                                             |                                                                                                                                                                                                                                                                                                                                  |
|--------------|---------------------------------------------------------------------------------------------------------------------------------------------------------------------------------------------------------------------------------------------------------------------------------------------|----------------------------------------------------------------------------------------------------------------------------------------------------------------------------------------------------------------------------------------------------------------------------------------------------------------------------------|
| Insufficient | Completely incorrect/Extremely vague information: the patient does not recall the technical term of the diagnosis and does not provide a logical description of it (both conditions are satisfied)                                                                                   | Examples: <> - (AF) <<My heart doesn't beat well>>, (DVT) <>                                                                                                                                                                                                             |
| Sufficient   | The patient does not recall the technical term of the diagnosis; However, he/she provides a description of it, which contains only some logical elements.                                                                                                                            | Examples: (AF) <<The heart beats irregularly, perhaps because I am anxious>>, (DVT) <>                                                                                                                                                          |
| Good         | The patient correctly recalls the technical term of his/her diagnosis, however he/she provides an incomplete/incorrect explanation of it - or –The patient provides an incomplete technical term of his/her medical condition, followed by a complete and logical description of it. | Examples: (AF) <> or <> (DVT) <> or <> |
| Very good    | Global/complete/correct description: the patient uses the technical term of the diagnosis and provides a logical description of it (both conditions must be satisfied).                                                                                                                     | Examples : (AF) <>, (DVT) <>                                                                                                                                     |

## Question 2

|              |                                                                                                                                                                                                                                                                                                                                                                                                                                                                                                                                     |  |
|--------------|-------------------------------------------------------------------------------------------------------------------------------------------------------------------------------------------------------------------------------------------------------------------------------------------------------------------------------------------------------------------------------------------------------------------------------------------------------------------------------------------------------------------------------------|--|
| Insufficient | 
The patient does not list any of the take-home medications prescribed
 
IF NO MEDICATIONS HAVE BEEN PRESCRIBED: The patient does not know at all whether or not new medications have been prescribed
                                                                                                                                                                                                                                                                                                                    |  |
| Sufficient   | 
The patient recalls only some of the take-home medications prescribed and he/she provides incorrect dosage/does not recall the dosage.
 
IF NO MEDICATIONS HAVE BEEN PRESCRIBED: The patient provides an irresolute answer. He/she may mistake regular/chronic medications for new ones.
                                                                                                                                                                                                                                |  |
| Good         | 
The patient lists all take-home medications but he/she does not remember their dosage; or The patient recalls the correct dosage of all medications but he/she cannot recall the name of all of them; or The patient correctly associates take-home medications with their dosage, however he/she does not remember all of them.
 
IF NO MEDICATIONS HAVE BEEN PRESCRIBED: The patient states that no new take-home medications have been prescribed, although he/she shows some hesitancy or insecurity.
 |  |
| Very good    | 
The patient lists all prescribed take-home medications and recalls the correct dosage for all of them.
 
IF NO MEDICATIONS HAVE BEEN PRESCRIBED: The patient knows for certain that no new take-home medications have been prescribed.
                                                                                                                                                                                                                                                                                  |  |

## Question 3a – (Please note: Take-home medications have been prescribed)

|              |                                                                                                                                                                                                                    |                                                                                                                                                                                                                                                                     |
|--------------|--------------------------------------------------------------------------------------------------------------------------------------------------------------------------------------------------------------------|---------------------------------------------------------------------------------------------------------------------------------------------------------------------------------------------------------------------------------------------------------------------|
| Insufficient | The patient does not know the purpose of the prescribed medications and does not know for how long he/she should take them.                                                                                        |                                                                                                                                                                                                                                                                     |
| Sufficient   | The patient knows either the purpose of the treatment or the duration of treatment or the technical term of the main complication of his/her condition (one of the three criteria must be satisfied) | Please note: the main complication is stroke for atrial fibrillation and pulmonary embolism for deep vein thrombosis.                                                                                                                                        |
| Good         | The patient knows two of the three criteria listed above (purpose of the medication/treatment duration/technical term of the main complication).                                                                   | 
Examples (AF) <<I have to inject heparin to make my blood thinner until I see a cardiologist, otherwise I could get worse>>
 
(DVT) <<I need to inject heparin to make my blood more fluid, in order to avoid a pulmonary embolism to
 |

|           |                                                                                                                                                      |                                                                                                                    |
|-----------|------------------------------------------------------------------------------------------------------------------------------------------------------|--------------------------------------------------------------------------------------------------------------------|
|           |                                                                                                                                                      | occur; I can't remember though for how long I should continue taking it>>.                                         |
| Very good | The patient shows knowledge in all the criteria listed above (purpose of the medication/treatment duration/technical term of the main complication). | Example (AF) <> |

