## Interventions

### *Study group*

All subjects enrolled in the study group are shown during the discharge process the video related to the patient's condition (DVT vs AF), using it as a graphic support to the doctor's verbal explanation of the diagnosed pathology and its potential main complication.

For the purposes of the study we have selected two video clips, available on various internet sites and not covered by any copyright restrictions; these have been modified and shortened to make them suitable to use in our study setting.

The clips last between 27 and 45 seconds and show the pathophysiological process underlying the two diseases under study, namely deep vein thrombosis and atrial fibrillation.

The SIs show the videos to patients on the institutional computer or, alternatively, on their personal smartphone / tablet (in any case in resolutions from 480 pixels to 720 pixels). The content of these video clips is adequate for adults with all levels of education. In addition to that, videos are purposely without audio content, as it is specifically requested that SIs provide explanations and comments according to what is shown on the screen, guiding patients during the vision of the clip. In particular, SIs are asked to structure the explanation as follows: a) describe the relevant anatomical structures and the physiological processes in normal conditions (lower limb veins and venous circulation/heart chambers and normal blood flow between atria and ventricles); b) describe the pathological process that determines formation of a blood clot in the respective anatomical sites (stagnation of blood in proximity of venous valves with formation of a thrombus/ fibrillation of the right atrium, stagnation of blood and formation of a thrombus in the atrium); c) describe the dislocation of the thrombus to reach the target anatomical site (lung/brain); d) describe the complications derived from clot's dislocation to the target anatomical site (pulmonary embolism/stroke). Although doctors follow the steps described above, which are based on the structure of the videos, we did not aim to standardize the linguistic style of their explanations. As an example, they could use the term "thrombus" or "clot" or any other synonym they believe is suitable for the comprehension of the patient, even recurring to street slang or dialectal forms if deemed appropriate.

Doctors can pause and rewind the clip at their discretion or if the patient requests to do so.

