### **Outcomes**

The main outcome will be patients' comprehension of the domains directly related to the video contents, i.e., knowledge of the *diagnosis* and its potential *complication*, corresponding to interview's questions 1-3-4 (see the attached file *Telephone Interview*).

Secondary outcomes will be the knowledge of the prescribed therapy and patients' satisfaction (see the attached file *Telephone Interview*).

The outcomes will be measured through a telephone interview, consisting of a set of questions specifically designed for the purposes of this study (see the attached file "*Telephone interview*"). The interview is made of six questions, focusing on the different domains of comprehension.

The telephone interview is conducted by one of the two researchers responsible for this task. Audio files are then stored on a computer and subsequently reexamined by both reviewers, who will assign a score to each question contained in the interview (see the attached file "*Telephone interview*").

We developed a scheme to aid the reviewers in the interpretation of patients' answers, to reduce reviewers' inter-operator variability (see the attached file *Interpretation of patients' answers*).

Patients' answers will receive a score on a 4-point Likert scale (ranging from zero to three) from low to high knowledge.

Scores from the two independent reviewers will be summed to obtain an overall score. The score for the main outcomes will therefore range: 0-18 for the main outcome (questions 1-3-4), 0-6 for the knowledge of the prescribed therapy (question 2), 0-12 for patient's satisfaction (questions 5-6).

To the best of our knowledge, no currently available validated questionnaires would serve for the purpose of our study, i.e., for the simultaneous measurement of different domains of comprehension across two different medical conditions.

Hence, we have developed the ad-hoc interview and its related interpretation scheme using face and content validity. Construct validation would require an amount of time and resources equivalent to that of the trial itself, pushing it beyond practical feasibility.

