### Telephone Interview

- 1. Could you tell me the name of the medical condition you have been diagnosed with and explain what it is in your own words?**

☐ Insufficient ☐ Sufficient ☐ Good ☐ Excellent

- 2. Have you been prescribed new take-home medications in the Emergency Department for this medical condition?**

☐ Insufficient ☐ Sufficient ☐ Good ☐ Excellent

- 3a). (For those patients who have been prescribed new take-home medications) What are these drugs for and for how long should you take them? What are the possible complications of your medical condition?**

☐ Insufficient ☐ Sufficient ☐ Good ☐ Excellent

- 3b). (For patients who have not been prescribed new take-home medications) Do you know why you have not been prescribed new medications? When are you going to have a follow-up visit? What are the possible complications of your medical condition?**

☐ Insufficient ☐ Sufficient ☐ Good ☐ Excellent

- 4. What symptoms would worry you enough to return to the Emergency Department?**

☐ Insufficient ☐ Sufficient ☐ Good ☐ Excellent

- 5. While in the Emergency Department did you get a chance to ask your doctor questions on your medical condition?**

☐ No, none of them ☐ Only a few of them ☐ Nearly all I had in mind ☐ Yes, all of them

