**Question 3b – (Please note: No take-home medications have been prescribed)**

|              |                                                                                                                                                                                                                                          |                                                                                                                                                                                                                                                                                     |
|--------------|------------------------------------------------------------------------------------------------------------------------------------------------------------------------------------------------------------------------------------------|-------------------------------------------------------------------------------------------------------------------------------------------------------------------------------------------------------------------------------------------------------------------------------------|
| Insufficient | The patient does not know why no therapy was prescribed; he/she does not know when the check-up will be; he/she does not know the technical term of the main complication of his/her medical condition (all three criteria must be met). |                                                                                                                                                                                                                                                                                     |
| Sufficient   | The patient shows knowledge in at least one of the three above-mentioned criteria.                                                                                                                                                       | Example: (AF) <>.                                                                   |

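### Primary-outcome scoring: Question 3a puts a patient who knows only the complication at both 0 and 1, and Question 1 leaves some answers without a level

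*Protocol*

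**What the plan says.** The protocol's Outcomes section defines the main outcome as knowledge of the diagnosis and its potential complication, "corresponding to interview's questions 1-3-4". Each answer is marked 0 to 3 by each of two reviewers and the marks are added, giving 0 to 18. The same section says that the interpretation scheme exists to limit variation between reviewers, and that construct validation was not feasible.

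Supplementary Data 4 sets the levels.

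- **Question 3a (drugs prescribed).** The lowest level, Insufficient, applies when "The patient does not know the purpose of the prescribed medications and does not know for how long he/she should take them". One level up, Sufficient needs only the purpose, or the duration, or "the technical term of the main complication of his/her condition (one of the three criteria must be satisfied". Good needs two of the three, Very good all three.
- **Question 3b (no drugs prescribed).** Insufficient needs all three items to be unknown, ending with "he/she does not know the technical term of the main complication of his/her medical condition (all three criteria must be met".
- **Question 1.** Insufficient: neither the term nor a logical description. Sufficient: no term. "However, he/she provides a description of it, which contains only" some logical elements. Good: the correct term with an incomplete or wrong explanation, or an incomplete term with a complete and logical description. Very good: both the term and a logical description.

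**The concern.** A scoring scheme for a primary endpoint should send each answer to exactly one level. Question 3a does not, and the answer it mishandles is one that the outcome is meant to credit. Knowledge of the complication is half of the outcome's definition, and the explanation that accompanies the video (Interventions, Study group) ends with the complication, while none of its four steps covers the purpose or duration of the drugs.

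Question 1 has the opposite fault: some foreseeable answers have no level, so each reviewer must invent one. The protocol describes neither a tie rule nor adjudication; the two marks are simply summed. At stake are extra disagreement between reviewers and, if such answers are scored low and occur more often in the video arm, a smaller measured difference.

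**Working it through.** **1. The plan's own figure.** From Sample size: control score 10, 20% higher with video, so a difference of 0.20 × 10 = 2 points; SD 4; two-sided 5%; 80% power. Normal approximation: n = 2 × (1.96 + 0.84)² × 4² / 2² ≈ 63 per arm. The t-based version gives 63.8, so 64. Allowing for 10% loss: 64 / 0.90 = 71.1, so 72. The stated 64 and 72 are reproduced, and the point does not change them.

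**2. Question 3a, all 2³ = 8 patterns of purpose, duration and complication term.**

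| Known | Levels met in 3a |
|---|---|
| none | 0 |
| complication term only | **0 and 1** |
| purpose only | 1 |
| duration only | 1 |
| any two (3 patterns) | 2 |
| all three | 3 |

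Seven of 8 patterns have one level and one has two. The overlap needs the technical term; a complication described only in lay words fits 0 alone. In 3b nobody who knows any criterion can fall in Insufficient. Its upper levels are worded cumulatively (at least one, at least two), so they work as a count once the highest level met is taken; on that reading all 8 patterns are unique.

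**3. Question 1, 3 states of the term × 3 states of the description.**

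| Term | Description absent or illogical | Some logical elements | Complete |
|---|---|---|---|
| none | 0 | 1 | **no level** |
| incomplete | **no level** | **no level** | 2 |
| correct | 2 | 2 | 3 |

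Three of 9 patterns have no level. Under Good, the second DVT example is a patient who reports a thrombosis and explains it as a clot blocking the arteries. The paired AF example shows that this slot illustrates the incomplete-term route, which requires a complete and logical description. Placing the clot in the arteries is wrong, so the example contradicts the rule.

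**4. Size for one patient.** One level × two reviewers = up to 2 of 18 points. If only one reviewer gives the lower mark, it is 1 point.

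**5. Size for the trial.** The documents do not say how many patients give complication-only answers, so the excess share x in the video arm is an assumption. If both reviewers score them 0 instead of 1, the mean difference falls by 2x. Power at 64 per arm is Φ(Δ / (4 × √(2/64)) − 1.96), with 4 × √(2/64) = 0.707.

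| Assumed excess x | Fall in difference | Δ | Power |
|---|---|---|---|
| 0 | 0 | 2.0 | 80.7% |
| 5% | 0.1 | 1.9 | 76.6% |
| 10% | 0.2 | 1.8 | 72.1% |
| 20% | 0.4 | 1.6 | 61.9% |
| 30% | 0.6 | 1.4 | 50.8% |

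With split marks, the fall is x instead of 2x.

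**The case against.** **The intended reading of 3a is easy to guess.** Sufficient names this very case, Good and Very good count two and three criteria, and 3b sets zero at none known. One row has lost a clause, and a reviewer who takes the highest level met would give 1. The same two instructed reviewers score every interview. This stands as a reason to expect limited harm. It does not supply the missing rule.

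**Question 1 can be partly rescued.** If an incomplete term counts as not recalling the term, two of the three gaps close, at 0 and 1. The complete description without a term still has no level, and the arteries example, listed at 2, would then sit higher than the rule allows.

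**An excess in the video arm is not shown.** A patient who has learned that a clot causes the complication may infer what the drug is for, and the 3a examples credit purpose generously. Such a patient scores 2 without ambiguity. This stands: the excess is plausible but could be nil.

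**Stronger conclusions that a reader might draw:**

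- *The ambiguity could create an effect.* The Blinding section intends the reviewers not to know the allocation. Scoring 1 follows the wording of Sufficient and credits real knowledge; scoring 0 dilutes. The documents show no route to a false difference.
- *Two points equals the whole planned effect.* That compares one patient's worst case with a difference between group means. Supplementary Data 5 reports a per-protocol difference of 2.65 (95% CI 1.39 to 3.91). Holding the standard error fixed, it would take an excess of about 1.39 / 2 = 70% to account for the distance from zero to the lower limit.
- *Question 2 has the same fault.* The form asks "Have you been prescribed new take-home medications in the Emergency Department for this medical condition", while the scheme gives zero when "The patient does not list any of the take-home medications prescribed". But Question 2 is a secondary outcome, and Roles and Responsibilities says the interviewers standardized their communication strategy beforehand, so improvised prompting is not established.
- *Lay terms should count, because doctors may explain by "even recurring to street slang or dialectal forms if deemed appropriate".* Question 1 asks for the name of the condition, and the complication is itself a named step of the explanation. Accepting lay equivalents would change what is measured; it would not repair a contradiction.

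**Conclusion.** The point holds for Questions 3a and 1, both part of the primary score. One of 8 patterns in 3a has two levels, 3 of 9 in Question 1 have none on a literal reading, and one example contradicts its own level. An affected answer can move a patient's total by up to 2 of 18 points when the doubt is one level for each reviewer.

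The effect on the trial cannot be derived from the documents. Under an assumed 10% excess in the video arm, all scored 0 on 3a by both reviewers, the mean difference falls by 0.2 point and power from about 81% to 72%. With no excess, the mean difference does not shift and what remains is reviewer disagreement. The figures use the normal approximation with SD 4. The supportable conclusion is added noise and possible dilution of a true effect, from rules that need only a wording change.

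**What to change.** - **Question 3a:** define Insufficient as none of the three criteria known, as in 3b, and state that the score is the number of criteria known. All 8 patterns then have one level, and the sentence also settles the cumulative wording of 3b.
- **Question 1:** assign each of the three missing patterns to a fixed level, chosen without sight of results by arm, and correct or move the arteries example.
- **Rescoring:** have both reviewers, still blinded to allocation, rescore the affected Question 1 and 3a answers from the stored recordings. Report the original and the rescored result.

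Supplementary Data 5 already analyses 137 patients reached and 144 in total, so rescoring now would follow the analysis. The Statistical methods section requires changes after database lock to be described in the study report, and this should be reported as one. Under the 3a correction, a complication-only answer scored 0 can only rise to 1, which is a further reason to disclose it.

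The cost is two edited scoring tables and a modest amount of reviewer time, for at most 137 recordings. Interview length is not given, so the hours cannot be stated. The sample size stays at 64 and 72 per arm.
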